### Plans to promote participant retention and follow-up {25b}

Retention will be promoted through regular household visits, community meetings, and reminder phone calls/WhatsApp messages before scheduled assessments. Monthly home visits will reinforce adherence, troubleshoot problems, and monitor compliance. Compliance will be assessed by Food diaries maintained by participants; Unannounced spot checks by field staff, and Monthly supervisory visits. Compliance is defined as use of the provided iron cookware for ≥ 1 main meal per day on ≥ 4 days per week, sustained for ≥ 70% of the intervention period. Participants not meeting this criterion will be considered non-compliant for per-protocol analysis but will remain in the intention-to-treat (ITT) analysis. Outcome data (Hb, ferritin, and other biomarkers) will be collected for all randomized participants, even if they discontinue or deviate from the intervention, unless consent is withdrawn entirely.

### Data management {26}

Data will be collected using paper-based case report forms (CRFs) and subsequently entered into a secure electronic database. To ensure accuracy and reliability, double data entry and validation will be performed, and range and consistency checks (e.g., hemoglobin values < 5 g/dL or > 18 g/dL) will be applied to identify implausible entries. Each participant will be assigned a unique coded identifier, with the linkage file maintained separately by the Principal Investigator in a password-protected system. Paper CRFs will be stored in locked cabinets accessible only to authorized staff, while electronic datasets will be encrypted and restricted to study personnel with appropriate clearance. Weekly data backups will be maintained on institutional servers. All personal identifiers will be removed prior to analysis, and no identifiable information will be disclosed in publications. A detailed data management standard operating procedure (SOP) will be archived and made available upon request.

### Statistical methods {27}

#### Primary and secondary outcomes {27a}

Descriptive statistics will be used to summarize baseline characteristics. Continuous variables will be expressed as mean (SD) or median (IQR) as appropriate, and categorical variables as frequencies and percentages. Baseline differences between intervention and control groups will be assessed using independent *t*-tests (or Mann–Whitney *U* tests for non-normal data) and chi-square or Fisher’s exact tests for categorical variables. Standardized mean differences (SMDs) will be calculated, with an SMD < 0.1 indicating adequate baseline balance.

Continuous outcomes such as haemoglobin (Hb), serum ferritin, soluble transferrin receptor (sTfR), and transferrin saturation (TSAT) will be analyzed using linear mixed-effects models with fixed effects for group, time, and group × time interaction, and random effects for participants (and clusters if applicable). Binary outcomes such as anaemia prevalence, adherence, and adverse events will be analyzed using mixed-effects logistic regression. Risk ratios, odds ratios, mean differences, and 95% confidence intervals will be reported. The significance level will be set at *p* < 0.05 (two-tailed). Analyses will be performed using R software.

To provide a comprehensive evaluation of iron status, additional biomarkers will be assessed, including total iron-binding capacity (TIBC), erythrocyte protoporphyrin, mean corpuscular volume (MCV), and C-reactive protein (CRP). These indicators will enable differentiation between iron deficiency, anaemia of inflammation, and other causes of low Hb. Effect size (Cohen’s d) will be calculated for the primary outcomes (Hb and ferritin) to quantify the magnitude of intervention impact**.**

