### Outcomes {16}

The outcome measures and assessment time points are summarized in Table 1. Blood samples will be collected at each time point for the biochemical analysis of iron status markers. Dietary intake and adherence to cookware use will be monitored using structured questionnaires and periodic household visits.

**Table 1 Tab1:** Summary of primary, secondary, and exploratory outcomes with measurement variables, analysis metrics, aggregation methods, and time points (baseline to 12 months)

Outcome type	Measurement variable	Analysis metric	Method of aggregation	Time points
Primary outcome	Serum ferritin (µg/L), CRP-adjusted	Mean change from baseline	Mean ± SD, mean difference (95% CI)	Baseline, 6 months, 12 months
Secondary outcomes	Haemoglobin (g/dL)	Mean change from baseline	Mean difference (95% CI)	Baseline, 6 months, 12 months
	Soluble transferrin receptor (mg/L)	Mean change from baseline	Mean difference (95% CI)	Baseline, 6 months, 12 months
	Transferrin saturation (%)	Mean change from baseline	Mean difference (95% CI)	Baseline, 6 months, 12 months
	Anaemia prevalence (Hb < 12 g/dL, WHO)	Proportion with anaemia	Risk difference, risk ratio (95% CI)	Baseline, 6 months, 12 months
	Nutrition knowledge and practice score	Change in score	Mean difference	Baseline, 6 months, 12 months
	Adherence to iron cookware use (≥ 1 main meal/day, ≥ 4 days/week)	Proportion adherent	Percentage adherence	Monthly monitoring; summarised at 6 months, 12 months
	Adverse events (GI symptoms, iron overload, other harms)	Proportion with ≥ 1 adverse event	Frequency counts, percentages	Ongoing; summarised at 3, 6, and 12 months
Exploratory outcomes	Cost-effectiveness (per unit Hb and ferritin increase)	Incremental cost-effectiveness ratio (ICER)	ICER	6 months, 12 months
	Dietary modifiers (vitamin C intake, tea/coffee, phytates)	Effect modification	Subgroup analyses	Baseline, 6 months, 12 months
	Subgroup analysis by baseline anaemia	Effect difference	Interaction tests	6 months, 12 months
	Community-level adoption of cookware post-trial	Proportion of households continuing usage	Adoption rate (%)	Endline at 12 months; post-trial sustainability follow-up

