### Participant timeline {18}

#### Sample size {19}

The sample size was calculated based on hemoglobin (Hb) as the key outcome variable. Considering a standard deviation (SD) of 1.2 g/dL and a minimum detectable difference (Δ) of 0.5 g/dL between the intervention and control groups, the required sample size was estimated to provide 80% power (*β* = 0.20) at a two-sided significance level of 5% (*α* = 0.05, 95% confidence level). The sample size was adjusted accordingly to account for an anticipated 10% attrition due to loss to follow-up, pregnancy, or withdrawal. The final required sample size is 202 participants, with 101 participants allocated to the intervention group and 101 participants to the control group [18, 19]. Since we will pool the data from two sites for the main outcome measures, the total sample size will be equally divided into two study sites.

The sampling strategy for this study involves a multi-stage approach to ensure methodological rigor and reduce potential biases. Initially, eligible villages will be purposefully selected from study areas based on predefined inclusion criteria such as population size, accessibility, and anemia prevalence data, if available. Within each selected village, a household listing will be conducted to identify households with at least one eligible non-pregnant, non-lactating (NPNL) woman of reproductive age. In instances where more than one eligible woman resides in a single household, one participant will be selected using simple random selection methods—such as a coin toss or random number generation—to prevent intra-household clustering and to maintain the independence of observations. This ensures that each household contributes only one participant to the study. Following this, the identified households will be subjected to block randomization, as previously described, to assign participants into intervention and control groups in balanced proportions. This sampling framework enables equitable group allocation, reduces selection bias, and ensures that the study sample is representative of the target population within the selected geographic context.

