### Additional analyses {27d}

Pre-specified subgroup analyses will assess effect modification by baseline anaemia status (anaemic vs non-anaemic), dietary iron intake categories, and CRP-adjusted vs unadjusted ferritin. Mixed-effects regression models will be applied with adjustment for covariates including age, body mass index (BMI), baseline iron status, dietary intake, inflammation (CRP), and socioeconomic status. Sensitivity analyses will test the robustness of results to exclusion of participants with elevated CRP, alternative adherence thresholds, and different imputation strategies. An exploratory cost-effectiveness analysis will be conducted, estimating the incremental cost per unit increase in haemoglobin (g/dL) and ferritin (µg/L).

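### The primary contrast is an unadjusted difference in change from baseline; adjusting for baseline would answer the same question more precisely from the same data

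*Protocol article*

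**What the plan says.** Three places in the protocol article bear on this.

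- **Outcomes {16}, Table 1.** The primary outcome is "Serum ferritin (µg/L), CRP-adjusted", with analysis metric "Mean change from baseline", at baseline, 6 and 12 months. The summary is an arithmetic mean with SD and a mean difference. Hb, sTfR and TSAT carry the same change metric as secondary outcomes.
- **Statistical methods {27a}.** The continuous outcomes "will be analyzed using linear mixed-effects models with fixed effects for group, time, and group" by time, with a random participant effect. The section states no baseline covariate, no equal-baseline constraint and no transformation.
- **Additional analyses {27d}.** "Mixed-effects regression models will be applied with adjustment for covariates including age, body mass index (BMI), baseline iron status" is the start of a longer covariate list. This is the only place where baseline level enters a model. The text does not say whether these are the 27a models with covariates added or separate ones.

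Sample size {19} rests on Hb: SD 1.2 g/dL, difference 0.5 g/dL, and "the required sample size was estimated to provide 80% power". The article gives no SD, correlation or target difference for ferritin.

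**The concern.** When baseline is one of the repeated outcomes and each arm has its own baseline mean, the group-by-time term at a follow-up visit compares the arms on change. The chance baseline difference is subtracted in full, with a coefficient of one, whatever the true correlation. Baseline adjustment subtracts only the part that predicts follow-up. It is therefore never less precise in large samples, and below ρ 0.5 the change contrast is noisier than ignoring baseline altogether.

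What is at stake is power for the primary outcome and for Hb, in a trial of 202 women sized for 80% power on Hb and with no stated power for ferritin. A smaller matter is that, if the 27d covariate list were added to the 27a model as it stands, baseline would be outcome and predictor in the same model.

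**Working it through.** **1. The plan's own figure.** Inputs from Sample size {19}: SD 1.2, difference 0.5, two-sided 5%, 80% power, 10% attrition.

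n per arm = 2 × (1.960 + 0.842)² × 1.2² / 0.5² = 90.4, so 91. Then 90.4 / 0.9 = 100.5, so 101 per arm and 202 in all. The stated total reproduces. About 91 per arm remain after attrition (101 × 0.9 = 90.9).

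**2. What the 27a contrast is.** In a random-intercept mixed model fitted to simulated complete data, the 12-month group-by-time estimate agreed with the difference in mean change to rounding error.

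**3. Relative variance.** Take variance σ² at both times and correlation ρ.

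- Change: 2σ²(1−ρ)
- Baseline-adjusted: σ²(1−ρ²)
- Ratio, adjusted to change: (1−ρ)(1+ρ) / [2(1−ρ)] = (1+ρ)/2

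The ratio is 0.75 at ρ 0.5, 0.85 at ρ 0.7 and 0.90 at ρ 0.8. It does not depend on the distribution of the marker.

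**4. Power for Hb.** Hb is used because it is the only outcome with stated inputs. Assumptions: 1.2 g/dL is the SD at one time point; ρ is unknown and is varied. The standard error is 1.2 × √(2/91) × √v = 0.1779 × √v, with v = 2(1−ρ) for change and v = 1−ρ² for the adjusted contrast. Power is approximately Φ(0.5/SE − 1.96); the noncentral t value is in brackets.

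| ρ | v, change | Power, change | v, adjusted | Power, adjusted |
|---|---|---|---|---|
| 0.4 | 1.20 | 72.8% (72.3%) | 0.84 | 86.6% (86.2%) |
| 0.5 | 1.00 | 80.2% (79.8%) | 0.75 | 90.1% (89.8%) |
| 0.7 | 0.60 | 95.2% (95.0%) | 0.51 | 97.6% (97.5%) |
| 0.8 | 0.40 | 99.4% (99.3%) | 0.36 | 99.7% (99.7%) |

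**5. The other reading of the SD.** If 1.2 g/dL were the SD of the change, the planned contrast would have its 80% by construction. The adjusted one would have SE = 0.1779 × √((1+ρ)/2), hence about 92% at ρ 0.4, 90% at ρ 0.5 and 86% at ρ 0.7. The gain stays; the shortfall below 80% does not.

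**6. Ferritin scale.** Everything here is assumed. Simulation with 90 per arm and 4,000 replicates, comparing raw change with log ferritin adjusted for baseline:

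- Lognormal, 30% proportional effect, ρ 0.5: 91% against 98% (log-SD 0.5), 60% against 82% (0.7), 33% against 60% (0.9), 21% against 46% (1.1).
- Gamma, coefficient of variation 0.8, ρ 0.65: 73% against 65% for a proportional effect, but 79% against 99.8% for an additive one.
- With no effect, the raw change analysis rejected in 4.2% to 5.4% of trials in every scenario.

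**The case against.** The strongest reply is that nothing here is an error. A difference in mean change in µg/L is a legitimate estimand, it is clear to readers, and its test holds its level. That stands.

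The reply continues that baseline adjustment is not absent, since 27d lists baseline iron status, and that the article announces a separate analysis plan where model details and any transformation may be set. This stands only in part. Silence on a transformation is no fault in an article, and whether 27d reuses the 27a model is simply not stated. But Table 1 and 27a do state the metric, the time points and the model terms, and together these make the unadjusted change the primary contrast.

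It can also be said that the gain is small when ρ is high. That is true: at ρ 0.8 the Hb gain is negligible.

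A reader might go further and infer that raw ferritin is the wrong scale, that the planned summary is invalid, and that a log analysis would clearly have more power. The documents do not support this. They give no ferritin distribution, SD or correlation. The raw analysis kept its type I error in simulation. The log advantage needs roughly lognormal data and reversed in a gamma case. A geometric mean ratio also answers a different question, while the exploratory cost-effectiveness analysis is per µg/L.

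**Conclusion.** The planned primary contrast is valid but gives up precision that the trial's own baseline samples would supply. The variance saving is 1 − (1+ρ)/2, that is 25%, 15% and 10% at ρ 0.5, 0.7 and 0.8, assuming equal variances at the two times. This half of the point needs no assumption about the shape of the ferritin distribution.

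For Hb, below ρ 0.5 the planned contrast falls short of the 80% for which the trial was sized, provided that 1.2 g/dL is the SD at a single visit. The adjusted contrast stays above 80% at every ρ, because its variance never exceeds σ², the value on which the 80% was computed.

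The size of the gain for ferritin cannot be given from the documents. The choice of ferritin scale is a secondary suggestion, not a defect.

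**What to change.** In 27a and Table 1, name the baseline-adjusted between-arm difference at each follow-up visit as the primary contrast for ferritin, and use the same form for Hb, sTfR and TSAT. Choose one of two forms and state it:

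- model the post-baseline values only, with baseline value by time as a covariate; or
- keep baseline as an outcome, constrain the arm means to be equal there, and use an unstructured covariance.

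The two agree closely with complete data but differ when baseline values are missing, so the choice should be explicit. In 27d, say that baseline is not entered as a covariate in any model where it is also an outcome.

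The cost is wording. No new data are needed. Because randomisation makes the baseline means equal in expectation, the adjusted contrast estimates the same mean difference in the same units as Table 1.

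Secondary step: fix the ferritin scale before outcome data are seen. Log ferritin with a geometric mean ratio is the natural choice if strong skew is expected. In that case the effect is read as a percentage, and the mean difference in µg/L should still be reported for the cost-effectiveness analysis, because back-transforming a ratio does not recover it.

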### Health education and behaviour change communication (BCC) sessions

The effectiveness of cooking with iron utensils will be evaluated alongside behaviour change communication (BCC) strategies, ensuring that participants adopt and sustain cooking practices that optimize iron absorption. To reinforce knowledge and promote long-term adherence, the study team will conduct group sessions and household visits, focusing on the role of dietary iron, i.e., understanding iron-rich food sources, factors that enhance absorption (e.g., vitamin C), and dietary inhibitors (e.g., tea, coffee, phytates); Anemia Prevention and Management which includes raising awareness about the consequences of iron deficiency and the importance of routine hemoglobin checks and Sustained Behaviour Change for encouraging the habitual use of iron cookware through community-driven approaches, including storytelling and role modelling by early adopters.

Participants in the intervention group will receive fortnightly group BCC sessions for the first 3 months, followed by monthly group sessions for the next 3 months (total, 9 group sessions over 6 months). In addition, monthly individual home visit sessions will be conducted throughout the 6-month intervention period to reinforce key messages, address practical barriers, monitor cookware usage, and offer personalized support. Each group session will last approximately 45–60 min, while home visits will be of 20–30 min duration, ensuring context-specific engagement and continuous motivation.

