### Data collection methods {25}

#### Plans for assessment and collection of outcomes {25a}

Data collection will include both quantitative and qualitative measures to evaluate iron status, dietary intake, adherence, and perceptions of the intervention. Quantitative data will be obtained through structured questionnaires to capture sociodemographic characteristics, health history, and dietary practices, as well as a 24-h dietary recall and Food Frequency Questionnaire (FFQ) to estimate dietary iron intake and food patterns. Laboratory investigations will be carried out at an NABL-accredited laboratory, where trained phlebotomists will collect blood samples for analysis of hemoglobin (Hb), serum ferritin, serum iron, soluble transferrin receptor (sTfR), transferrin saturation (TSAT), total iron binding capacity (TIBC), C-reactive protein (CRP), erythrocyte protoporphyrin, and mean corpuscular volume (MCV). These parameters will be measured at baseline, 6 months, and 12 months, with Hb and ferritin additionally assessed at 3 months. Duplicate testing will be performed on 10% of samples to ensure validity. Qualitative data will be collected through semi-structured interviews and focus group discussions (FGDs) to explore perceptions, facilitators, and barriers to cookware adoption and BCC acceptability, supplemented by field observations recorded during household visits to triangulate adherence and contextual factors. All assessors and laboratory staff will be trained and blinded to group allocation, and standard operating procedures (SOPs) will be followed at all stages to ensure consistency and data quality.

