### Missing data {27c}

Missing outcome data will be addressed using maximum likelihood estimation under the missing-at-random assumption. Multiple imputation with 20 datasets will be performed as a sensitivity analysis. Reasons for missingness (e.g., pregnancy, migration, withdrawal) will be documented. Additional sensitivity analyses will include complete-case analysis and per-protocol analysis to evaluate robustness of findings.

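### If the mixed model's participant effect is a random intercept, as ordinarily read, and within-woman correlation falls with time, the 12-month standard error is too small

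*Protocol article*

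**What the plan says.** Primary and secondary outcomes {27a} gives one model for Hb, ferritin, soluble transferrin receptor and transferrin saturation: "linear mixed-effects models with fixed effects for group, time, and group × time interaction, and random effects for participants". A bracket adds clusters where applicable. The section mentions no time slope, residual covariance or heterogeneous variance.

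Table 1 under Outcomes {16} gives the metric for ferritin (primary) and Hb as "Mean change from baseline", with mean differences and 95% CIs, at baseline, 6 and 12 months. Section 25a says the blood markers are "measured at baseline, 6 months, and 12 months, with Hb and ferritin additionally assessed at 3 months". The data for the two main markers may therefore have three or four visits, unequally spaced.

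Missing data {27c} relies on "maximum likelihood estimation under the missing-at-random assumption". The sensitivity analyses in 27c and 27d vary the imputation, the analysis population, the handling of raised CRP and the adherence threshold. None varies the covariance.

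**The concern.** Participants are listed beside clusters as grouping factors, and no slope is mentioned. Most analysts would fit that as a random intercept per woman. A random intercept with independent residuals implies compound symmetry: the correlation between baseline and month 12 is taken to equal that between baseline and month 3.

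The variance of a change from baseline depends directly on the correlation with baseline. Compound symmetry replaces each visit's own correlation by the average over all pairs. Every change-from-baseline contrast then gets the same standard error, whatever its distance from baseline. If repeated measurements of ferritin or Hb grow less alike as the gap lengthens, the longest contrast is given too small a standard error. The 12-month result for the primary outcome would then carry an interval that is too narrow and a false-positive rate above the stated 5%.

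**Working it through.** **Inputs.** Visits 0/6/12 (Table 1) or 0/3/6/12 (25a). Two-sided 5% and Hb SD 1.2 g/dL (Sample size {19}). About 91 women per arm after 10% attrition (101 × 0.9 = 90.9). Within-woman correlations are **assumed**, because the document gives none. The main range is 0.3 to 0.9 for visits 6 months apart, decaying exponentially, with some other patterns added.

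**The plan's own figure.** The formula 2 × (1.2 × (1.96 + 0.84)/0.5)² gives 90.4 per arm with unrounded normal quantiles. Then 90.4/0.9 = 100.5, rounded up to 101 per arm and 202 in total. The stated size reproduces. It compares two means with no repeated-measures correlation, so this point does not affect it.

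**Formula.** With balanced data, categorical time and equal variances:
- variance of a change under a random intercept ∝ 2(1 − mean pairwise correlation);
- true variance of the change to visit t ∝ 2(1 − correlation of baseline with t);
- model SE / true SE = √[(1 − mean correlation)/(1 − corr(0,t))];
- real type I error = P(|Z| > 1.96 × ratio).

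**Worked case, visits 0/6/12, correlation 0.70 at 6 months apart and 0.50 at 12.** Mean = (0.70 + 0.70 + 0.50)/3 = 0.633.
- 12 months: √(0.367/0.50) = 0.856; error 9.3%.
- 6 months: √(0.367/0.30) = 1.106; error 3.0%.

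**Other patterns with three visits, at 12 months.**
- 0.80/0.60: mean 0.733, ratio √(0.267/0.40) = 0.816, error 11.0%.
- 0.70/0.60: mean 0.667, ratio √(0.333/0.40) = 0.913, error 7.4%.

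**Exponential decay: SE ratio (type I error).**

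| 6-month correlation | 0/6/12: month 6 | 0/6/12: month 12 | 0/3/6/12: month 3 | 0/3/6/12: month 6 | 0/3/6/12: month 12 |
|---|---|---|---|---|---|
| 0.3 | 1.05 (4.0%) | 0.92 (7.1%) | 1.22 (1.7%) | 0.98 (5.4%) | 0.86 (9.1%) |
| 0.5 | 1.08 (3.4%) | 0.88 (8.4%) | 1.30 (1.1%) | 1.00 (5.1%) | 0.81 (11.1%) |
| 0.7 | 1.11 (2.9%) | 0.85 (9.5%) | 1.37 (0.7%) | 1.01 (4.7%) | 0.78 (12.7%) |
| 0.8 | 1.13 (2.7%) | 0.84 (10.0%) | 1.41 (0.6%) | 1.02 (4.5%) | 0.76 (13.5%) |
| 0.9 | 1.14 (2.5%) | 0.83 (10.5%) | 1.44 (0.5%) | 1.03 (4.3%) | 0.75 (14.2%) |

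Milder decay with four visits: take 0.75, 0.70, 0.65 and 0.60 at gaps of 3, 6, 9 and 12 months. Mean = (0.75 + 0.70 + 0.60 + 0.75 + 0.65 + 0.70)/6 = 0.692. The 12-month ratio is √(0.308/0.40) = 0.878, error 8.5%.

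**Patterns without decay from baseline.**
- Equal correlation at every gap: ratio 1.00 at every visit, no harm.
- Baseline correlated 0.5 with both follow-ups, and the follow-ups 0.7 with each other: mean 0.567, ratio √(0.433/0.50) = 0.93 at both 6 and 12 months, error 6.8%.

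**Checks by simulation.** In 8,000 simulated trials per scenario, the random-intercept standard error gave 9.4% at 12 months in the 0.70/0.50 case. An unstructured covariance gave 4.7% to 5.3%. REML fits with a random intercept **and slope**, at 6-month correlations 0.5 and 0.7, gave SE ratios of 0.98 to 1.02 with three visits. With four visits they gave 1.10 to 1.12 at month 3, 0.94 to 0.96 at month 6 and 1.02 to 1.05 at month 12.

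**The case against.** The strongest objection is that the text never says random intercept only. The plural wording allows a slope, and a slope removes the 12-month understatement in the fits above. The covariance structure, the coding of time and the degrees of freedom are commonly left to an SAP, and this trial's SAP is not shown. This stands as a limit on the point. It does not dispose of it, because 27a does state a random structure and its ordinary reading is the restrictive one.

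Second, the correlations are assumed. This also stands, and equal correlation would do no harm. The end of the BCC sessions at month 6 does not prove decay: it bears on the mean in one arm, and the control arm receives no BCC.

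A reader might go further and infer three things that the document does not support.
- *That the model is wrong at 6 and 12 months in opposite directions.* With month 3 in the model, the 6-month ratio under exponential decay is 0.98 to 1.03, which is essentially right. The over-wide interval is then at month 3. In the pattern where baseline stands apart, the 6-month standard error is too small.
- *That the 12-month interval is too narrow as a matter of fact.* That needs both an intercept-only fit and correlation that falls with time.
- *That group × time is a single straight-line slope.* 27a does not say that time is numeric, and Table 1 names discrete visits.

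**Conclusion.** The point holds conditionally. If 27a is fitted as a random intercept and correlation falls with time, the 12-month standard error for change in ferritin and Hb is 8% to 17% too small with three visits and 14% to 25% too small with four (exponential decay, 6-month correlation 0.3 to 0.9). Adding the other decaying patterns worked above, the real type I error at 12 months is about 7% to 11% with three visits and about 8% to 14% with four. At 6 months the standard error is 5% to 14% too large with three visits under exponential decay, and about right with four.

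These figures assume complete balanced data, equal variances and about 91 women per arm. There is also a reason that does not depend on the size of the error: with attrition expected, maximum likelihood under missing at random relies on a well-specified covariance, so a wrong one can affect the estimates as well. If the SAP already names a suitable structure, the point is answered.

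**What to change.** For continuous outcomes, replace the bare reference to participant random effects in 27a, and carry the same text into the SAP, along these lines:

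*Visit will be a categorical factor. Within-woman dependence will be modelled by an unstructured covariance matrix, with Kenward-Roger or Satterthwaite degrees of freedom. The arm difference in change from baseline will be estimated at the named visit. Any cluster effect will be added to this model.*

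State also whether the month-3 values of Hb and ferritin enter the model.

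The cost is one or two sentences and a few more covariance parameters: 6 for three visits (3 × 4/2) or 10 for four (4 × 5/2), against 2 for a random intercept with residual. With 202 women randomised, and about 182 after the planned attrition, these can be estimated comfortably. No extra data, visits or participants are needed.

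### The protocol contradicts itself on whether ferritin, haemoglobin or both are primary, and names neither a primary time point nor a deciding contrast

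*Protocol article*

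**What the plan says.** - **Outcomes {16}, Table 1.** The primary row holds one variable, CRP-adjusted serum ferritin, as mean change from baseline. Hb is the first secondary row. Both rows give baseline, 6 months and 12 months, and neither follow-up time is marked as primary.
- **Statistical methods, Primary and secondary outcomes {27a}.** Each continuous outcome gets a linear mixed model with group, time and their interaction. One level is set for everything: "The significance level will be set at *p* < 0.05 (two-tailed"). The section closes by saying that Cohen's d "will be calculated for the primary outcomes (Hb and ferritin) to quantify the magnitude of intervention impact".
- **Sample size {19}.** Hb is called the key outcome variable. The inputs are given as "Considering a standard deviation (SD) of 1.2 g/dL and a minimum detectable difference (Δ) of 0.5 g/dL", and "the required sample size was estimated to provide 80% power" at two-sided 5%. After 10% attrition the total is 202. No time point is given, and no ferritin SD or difference.
- **Plans for assessment and collection of outcomes {25a}.** The full panel, including CRP, is measured at baseline, 6 and 12 months, "with Hb and ferritin additionally assessed at 3 months". CRP is not among the extra 3-month measurements.
- **Health education and BCC sessions.** Group sessions end after six months, and "monthly individual home visit sessions will be conducted throughout the 6-month intervention period".

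**The concern.** The primary outcome, its time and its contrast together define the one claim that the 5% level protects. Here three sections give three answers: ferritin alone (Table 1), Hb and ferritin (27a), and Hb (sample size). They cannot all stand.

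The two follow-up times are not interchangeable either. Month 6 closes the period of counselling support, and month 12 comes six months after it. A difference at one and not at the other would mean different things.

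Two consequences follow. A null ferritin result could be reported as a positive trial on Hb, or the reverse, with a protocol section to cite either way. And if ferritin is the primary outcome, the stated 80% power does not describe the primary analysis, because it was worked out for Hb.

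**Working it through.** **1. Reproduce the stated sample size.** Inputs from Sample size {19}: SD 1.2 g/dL, difference 0.5 g/dL, two-sided 5%, 80% power, 10% attrition.

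n per arm = 2 × [1.2 × (1.960 + 0.842) / 0.5]² = 90.42

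90.42 / 0.9 = 100.5, so 101 per arm and 202 in total. This matches. (Rounding up to 91 before inflating gives 102 per arm and 204, an immaterial difference.) So 202 is the size for a single Hb contrast at the full 5% level.

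**2. Count the candidate tests.**
- Table 1 reading: ferritin at 6 and 12 months, two tests.
- Section 27a reading with each time tested separately: Hb and ferritin at 6 and 12 months, four tests.
- Section 27a reading with one joint test per outcome: two tests.

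**3. False-positive rate if success on any one counts, each test at two-sided 0.05.**

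Independent tests: 1 − 0.95² = 9.75% for two, and 1 − 0.95⁴ = 18.5% for four.

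Correlated tests: the share of 2 million simulated sets of correlated standard normal statistics in which the largest absolute value exceeds 1.960. For four tests, the correlation across both outcome and time is the product of the two correlations. All correlations are assumptions.

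| Tests | Correlation between times | Correlation between outcomes | False-positive rate |
|---|---|---|---|
| 4 | 0 | 0 | 18.5% |
| 4 | 0.5 | 0.3 | 16.9% |
| 4 | 0.7 | 0.3 | 15.6% |
| 4 | 0.8 | 0.3 | 14.6% |
| 4 | 0.9 | 0.7 | 11.6% |

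| Tests | Correlation between the two | False-positive rate |
|---|---|---|
| 2 | 0 | 9.75% |
| 2 | 0.5 | 9.1% |
| 2 | 0.7 | 8.3% |
| 2 | 0.9 | 7.0% |

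The range is therefore about 12% to 18.5% for four tests and about 7% to 9.75% for two.

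**4. What it would cost to keep several primary tests.** Step 1 repeated on the Hb inputs with a Bonferroni split, rounding up before inflating for attrition:
- Two tests at 0.025: 110 per arm; 110 / 0.9 = 122.2, so 123 per arm and 246 in total.
- Four tests at 0.0125: 129 per arm; 129 / 0.9 = 143.3, so 144 per arm and 288 in total.

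With 91 completers per arm, Hb power is 80% at 0.05, 72% at 0.025 and 62% at 0.0125. Nothing similar can be computed for ferritin, because the protocol gives no SD or difference for it.

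**The case against.** **The SAP may settle it.** The protocol refers to a SAP that is not shown. A testing order, a multiplicity rule and the exact model contrast often sit there, so their absence here is not in itself a fault. This stands. It does not remove the contradiction: whichever outcome the SAP names, at least one section of the protocol disagrees with it.

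**The sentence in 27a concerns a descriptive effect size.** True: it states no success rule. But it gives Hb primary status in the section that governs the analysis, and the sample size section also treats Hb as the key outcome. It is hard to set aside as a slip.

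**A reader might infer that the false-positive rate is about three times the stated 5%.** The documents do not support that as a fact. It needs four separate tests with success on any one, and no section states that rule. On Table 1's reading, or with one joint test per outcome, the inflation is at most about twofold. If both outcomes had to succeed, having two of them would add none.

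**A reader might infer that a joint group-by-time test loses power against a single contrast.** This does not hold in general. Take a single contrast with 80% power, so a noncentrality of (1.960 + 0.842)² = 7.85, and correlation 0.5 to 0.7 between times. The two-degree-of-freedom test then has 78% to 83% power when the effect is equal at both times, and 83% to 95% when it lies at one time only. The 71% obtained by leaving the noncentrality at 7.85 is a floor.

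**A reader might count 3 months as a further primary time.** Table 1 limits the primary outcome to 6 and 12 months, so it is not counted here.

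**Does the protocol favour 6 months?** No. The six-month intervention period is described in the BCC section, while Table 1 follows cookware adherence to 12 months. The choice of time belongs to the investigators.

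**Conclusion.** The point holds as an internal contradiction. The protocol gives incompatible statements of its primary outcome, leaves the primary time open, and sets a single 5% level without saying which contrast it applies to. This much rests on the text alone.

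The numerical size is conditional. It assumes that any one success would count as a positive trial and that the correlations lie between 0 and 0.9 across times and between 0 and 0.7 across outcomes. A single pre-stated contrast would bring the rate back to 5%. The stated total of 202 is arithmetically sound, but it supports 80% power for one Hb contrast only.

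**What to change.** Before recruitment, which Trial status gives as starting in December 2025:

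1. Name one primary outcome, one primary time point and the single between-arm model contrast at that time, tested at two-sided 5%.
2. Make Table 1, Sample size {19}, section 27a and the registry entry say the same.
   - If ferritin stays primary, reword 27a so that Hb is secondary. State in the sample size section that 202 gives 80% power for Hb only, and give the power for ferritin from an explicit SD and difference.
   - If Hb is made primary, 202 stands and Table 1 changes.
3. Test the remaining ferritin and Hb contrasts in a pre-stated order, or report them with confidence intervals and no confirmatory claim. In choosing an order, note that ranking both ferritin tests first would put Hb, the only outcome that was sized, behind two tests of unknown power.
4. State that the 3-month ferritin, which has no scheduled CRP, is not part of the CRP-adjusted primary analysis.

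**Cost.** If Hb is chosen, the change is wording in the protocol, SAP and registry. If ferritin is chosen, it also needs a ferritin power calculation, which may show that 202 is not enough. Under a fixed order, the later claims become conditional on the earlier ones, which is a small loss. Keeping more than one primary test with a split level would need about 246 participants (two tests) or 288 (four tests) on the Hb inputs.
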